### Safety

The trial is monitored monthly by an international steering committee and twice a year by a national steering committee where any adverse events are presented. We also planned a field visit by the national steering committee during the enrolment phase. The data safety and monitoring board (DSMB) for this trial did not request any interim analysis, but security analyses are planned after 500 and 1500 inclusions and will consist in comparing across study arms mortality, hospitalisation, and life-threatening events rates. The DSMB will meet at least twice during the recruitment phase to make recommendations following the security analysis. The ethics committees did not require any meetings during the active phase.

A child included in one of the two intervention arms could be removed from the study if (s)he experiences two consecutive episodes of > 5% weight loss during the course of treatment and is hospitalised once, or if (s)he is not SAM at inclusion but deteriorates to SAM during RUTF supplementation.

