### Trial design and study period

This study is a non-inferiority individually randomised controlled clinical trial conducted at the health centre level and in the community. Participants are randomly assigned to either the OptiMA or ComPAS strategy arms (intervention = OptiMA or ComPAS) or the national standard protocol arm (control = standard). Inclusions started on March 23, 2021, for a 9-month period with an expected end in December 2021. All participants are followed for a 6-month period post-randomisation, with an active phase expected to end in June 2022.

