In the control arm, children included with a MUAC < 115 mm and/or WHZ < − 3 and/or nutritional oedema are treated weekly with RUTF, according to the Niger national protocol dosage table based on the child’s weight. The Niger protocol provides a RUTF daily caloric intake of 150–200 kcal/kg/day during the entire treatment schedule until recovery in children with SAM. Children under 2 years old included with a MUAC between 115 and124 mm and WHZ > − 3 without bipedal oedema are treated weekly by one sachet of RUSF per day (500 kcal/day) during the course of treatment. However, children over 2 years old meeting the same moderate anthropometric criteria are not eligible for supplementation according to the national MAM programme.

The simplified strategies apply to AM children defined as MUAC < 125 mm or bipedal oedema (+, ++) without medical complications on admission and with a good or moderate appetite test.

In contrast to the weight-based RUTF ration in the national SAM programme, the OptiMA RUTF ration is calibrated to the child’s degree of wasting based on the combination of MUAC status and weight. Thus, more nutritional support is given to the most severely malnourished children and then gradually reduced as the child’s MUAC increased. Children with MUAC < 115 mm or oedema receive 175 kcal/kg per day of RUTF. Children with MUAC 115–119 mm, either at admission or during the course of treatment, receive 125 kcal/kg per day of RUTF, and children with MUAC ≥ 120 mm receive 75 kcal/kg per day of RUTF (with a minimum of one sachet/day) until discharge from the programme.

The ComPAS strategy is the most simplified protocol, not requiring a dosage table and proposing to gradually reduce the dosage according to the child’s MUAC status only during the outpatient follow-up as follows: 2 sachets/day of RUTF to children with MUAC < 115 mm or oedema and 1 sachet/day for children in the 115–124 mm MUAC zone.

For both simplified strategies, children with oedema receive the same RUTF ration as children with MUAC < 115 mm until oedema are resolved, at which point their ration is determined by MUAC and weight.

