### Follow-up

Table 3 summarises participants’ follow-up during the trial. All participants are monitored for a 6-month period post-randomisation. During the treatment phase, all children are followed once a week in outpatient consultations in each arm. On discharge from treatment, or immediately after inclusion for MAM children aged over 2 years in the standard arm, children are consulted once a month at home until the 6 months post-inclusion is completed. During village visits, a nurse research officer assisted by one or two CHWs monitored the anthropometric and clinical status of these children, referring any child who needed nutritional or medical care to either the primary healthcare facility or to the Mirriah hospital.

**Table 3 Tab3:** Schedule of enrolment, interventions, and assessments, OptiMA Niger

	Admission	Outpatient follow-up	Home visits	6-month post randomisation
Timeline	d0	4–16 weeks^1^	2–5 months^2^	
Frequency	Day	Weekly	Monthly	

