**Assessments**				
Nutritional and medical assessment	x	x	x	x
Hospitalisation if required		x	x	x
Adverse event		x	x	x

^1^Minimum of 4 weeks of RUTF supplementation and a maximum of 16 weeks for the first episode of AM and if relapse

^2^After discharge from the outpatient visit or for children not eligible for supplementation (standard arm aged 24–59 months with a MUAC 115–124 mm and WHZ > − 3 and no oedema)

^3^At the discharge outpatient visit

Failure to reach recovery criteria is defined after 16 weeks in the programme, then children are discharged from OTF as non-responders and consulted once a month at home until they reach the 6-month post-inclusion. For each non-responder discharged with a MUAC < 115 mm, a medical committee meets to decide on the medical follow-up of the child in the trial. Defaulters are defined as a child absent for 3 consecutive visits. CHWs trace children who are absent to motivate caretakers to return to the health facilities. If caretaker refuse to return to the health centre, the child is followed up once a month at home until the 6-month post inclusion period. When caretakers refuse the follow-up at home, the exit status of children is declared “confirmed defaulter” when the vital status is known and “lost to follow-up” when the vital status is unknown.

Children are discharged from outpatient treatment according to the anthropometric exit criteria of their allocation arm. In standard protocol, children need to achieve a MUAC ≥ 125 mm and a WHZ ≥ − 2 without oedema for two consecutive weeks while in OptiMA and ComPAS strategies, children will be discharged if they reach a MUAC ≥ 125 mm without oedema for two consecutive weeks. For each arm, all children will have to participate a minimum of 4 weeks in the programme with good clinical health (absence of fever) to be discharged from the OTF.

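### Safety section lets deteriorating children in the OptiMA and ComPAS arms alone be removed from the study, which conflicts with 6-month follow-up of all participants; the text should say they leave the ration and stay in follow-up

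*Protocol article*

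**What the plan says.** The Safety section of the protocol article states: "A child included in one of the two intervention arms could be removed from the study". There are two triggers:

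- **Trigger 1:** two consecutive episodes of more than 5% weight loss during treatment, together with one hospitalisation.
- **Trigger 2:** the child "is not SAM at inclusion but deteriorates to SAM during RUTF supplementation".

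The rule is permissive and names only OptiMA and ComPAS. The same section plans safety analyses after 500 and 1500 inclusions, "comparing across study arms mortality, hospitalisation, and life-threatening events rates".

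Elsewhere the article promises complete follow-up without exception. Trial design and study period: "All participants are followed for a 6-month period post-randomisation". Follow-up: "All participants are monitored for a 6-month period post-randomisation". The text after Table 3 separates leaving treatment from leaving the study. Non-responders are discharged from outpatient treatment and then "consulted once a month at home until they reach the 6-month post-inclusion". For defaulters whose caretaker will not return to the health centre, "the child is followed up once a month at home until the 6-month post inclusion period". Only refusal of home follow-up as well ends observation.

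Under Study outcomes, the primary outcome is measured at 6 months and any child who does not meet all the favourable criteria is unfavourable. Recovery is measured throughout the 6 months.

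**The concern.** Both triggers are signs of a poor course, so removal is informative. It applies on the experimental side only, and it is discretionary in an open-label trial. Trigger 2 as worded could not reach non-SAM children in the standard arm in any case. Those under 2 years receive RUSF, and "children over 2 years old meeting the same moderate anthropometric criteria are not eligible for supplementation".

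If removal from the study means that visits stop, the trial loses the 6-month status and later events of some of its highest-risk children in the two arms that test reduced rations. An analysis plan can choose how to treat such gaps, but it cannot restore visits that were never made. Two things are at stake: the power of the primary comparison, and the completeness of the between-arm safety comparison.

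**Working it through.** **1. What could go uncollected, on the literal reading.**

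| Information | Trigger 1 child | Trigger 2 child |
|---|---|---|
| 6-month primary status | lost | lost |
| Recovery after removal | lost | lost |
| Death or life-threatening event after removal | lost | lost |
| At least one hospitalisation (Table 1 outcome) | already recorded, since the trigger requires it | lost if the first admission comes after removal |

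Missing deaths and events can only lower the counts in the intervention arms. For the tabulated hospitalisation outcome, the gap is confined to trigger 2 children not yet hospitalised.

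**2. The plan's own sample size.** Inputs from Sample size and Statistical analysis: 68% favourable in each arm, margin 10 points, one-sided alpha 1.25% (z = 2.2414), power 90% (z = 1.2816), 5% inflation.

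n = (2.2414 + 1.2816)² × 2 × 0.68 × 0.32 / 0.10² = 540.1, so 541 per arm. 541 × 1.05 = 568, the stated figure. These numbers are not in dispute.

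**3. Removed children counted as unfavourable (intention-to-treat).** The article gives no removal rate. Assume that r = 2% or 5% of an intervention arm is removed and that a quarter of them would have been favourable. The true rate is 68% in both arms.

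p1 = 0.68 − 0.25r; SE = √[p1(1 − p1)/n + 0.68 × 0.32/n]; power = Φ((p1 − 0.68 + 0.10)/SE − 2.2414).

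| r | p1 | Power, n = 541 | Power, n = 568 |
|---|---|---|---|
| 0 | 0.6800 | 90.0% | 91.5% |
| 2% | 0.6750 | 86.5% | 88.2% |
| 5% | 0.6675 | 79.6% | 81.7% |

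The 568 column applies if every child without a confirmed favourable outcome is classed as unfavourable, because then nobody is unusable. The 541 column applies if the planned 5% is lost. At 541 per arm, 2% and 5% are about 11 and 27 children. Error at the margin stays at or below 1.25%, because counting failures against the intervention can only lower its rate.

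**4. Removed children dropped.** Take a true 58% against 68%, n0 = 541, n1 = 541(1 − r), and let a fraction f of the removed children be true failures.

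p1 = (0.58 − r(1 − f))/(1 − r).

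| r | f | p1 | Error in that analysis alone |
|---|---|---|---|
| 2% | 0.75 | 0.5867 | 2.2% |
| 2% | 1.00 | 0.5918 | 3.3% |
| 5% | 0.75 | 0.5974 | 4.9% |
| 5% | 1.00 | 0.6105 | 11.4% |

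**5. Both analyses required.** The chance that both succeed cannot exceed the chance that intention-to-treat succeeds, so the joint error is at most 1.25% in large-sample terms. Simulation with 5% removed (1,000,000 trials per case) gives a joint error of 1.22% if all removed children would have failed and 0.38% if 75% would have. Joint power at 68% in both arms, with a quarter otherwise successes, is 79.7%. Intention-to-treat is the binding analysis.

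**The case against.** The best defence is that the sentence is loose wording. The follow-up promise is stated twice without exception, and non-responders and most defaulters stay under home visits. Read with those statements, leaving the ration is at least as plausible as leaving follow-up. The article condenses a full protocol (version 2.0, available on request) that may settle the matter. This stands: data loss is one reading, not an established fact. It does not remove the point, because the published sentence says the study, and nothing in the article says that removed children continue to be seen.

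A reader might infer three stronger things that the document does not support:

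- **That a rescue rule limited to the intervention arms is itself wrong.** It has a sound rationale. Those arms receive reduced rations, while SAM children in the standard arm already receive the full national dose.
- **That the rule inflates the false-positive rate of the trial.** That needs removed children to be dropped and that analysis to decide alone. The Statistical analysis section plans both intention-to-treat and per-protocol, although it does not say outright that both must succeed.
- **That the whole hospitalisation comparison is compromised.** Trigger 1 children have already met the tabulated outcome.

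It is also fair to say that the removal rates and the quarter are chosen, and that the article offers nothing to anchor them.

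**Conclusion.** The point holds as a wording fault worth correcting. Taken literally, the removal rule contradicts follow-up of all participants and could leave informative outcome and safety data uncollected on one side only. The number of children affected is unknown.

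Under the assumed 2–5% removal with a quarter otherwise successful, the cost is power: from about 90–91% to about 86–88% (2%) or 80–82% (5%). Bias towards non-inferiority arises only in an analysis that drops these children. It does not carry through to the overall claim if both analyses must succeed. The safety gap covers later deaths and life-threatening events, and first hospitalisations among trigger 2 children not yet admitted.

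If the full protocol already keeps these children in follow-up, only the article's sentence needs correcting.

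**What to change.** In the Safety section, replace removal from the study with: *may leave the allocated ration for rescue treatment and stays in follow-up to 6 months*. State that the child is analysed in the allocated arm under intention-to-treat with the observed outcome, and that later deaths, hospitalisations and life-threatening events stay in the between-arm safety comparison.

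The cost is close to nil. The monthly home visit to 6 months is already planned for all children, so no new type of visit is added, and the sample size is unchanged.

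A sensitivity analysis that counts the same deterioration events as unfavourable in all three arms is optional. It belongs in the SAP, as does the per-protocol handling.

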### Ethics and dissemination

The study is conducted in accordance with the Declaration of Helsinki. We obtained ethical approval with annual renewal from the National Ethics Committee in Niger (065/2020/CNERS) and from the Ethics Evaluation Committee of the Inserm in France (CD/EB 21-025). The final version of the protocol, version 2.0, dated December 15, 2020, is available for sharing upon request and included minor amendments to the protocol version 1.0 which was approved by these two ethics committees and did not require a new authorisation. All data are anonymised when entered into the database using unique identification numbers. We intend to disseminate the results regardless of positive or negative findings via peer-reviewed publications, conferences, and clinical networks targeting academics, policy-makers, clinicians, and caregivers.

## Discussion

The OptiMA Niger trial presents a unique opportunity to generate much-needed evidence on various RUTF dosing strategies using the most robust trial design by individually randomising acutely malnourished children. This trial monitors the outcomes for an extended period of 6 months post-randomisation to capture recovery and relapse in the main outcome. This is also the first trial planning to evaluate the impact of reduced dose on the most vulnerable children (MUAC < 115 mm or oedema).

Should the ComPAS strategy be shown to be non-inferior to the current national protocol or OptiMA, this would provide the evidence for developing a more efficient nutrition protocol that could be implemented throughout the health system pyramid, beginning with CHWs. If OptiMA and ComPAS will be non-inferior to national protocol with respect to recovery rate for children with MUAC < 115 mm, the sample size will be sufficient to test whether OptiMA is in fact superior to ComPAS. If non-inferiority of ComPAS and OptiMA versus national protocol will not be demonstrated in each objective, then dose reduction will not be advisable for these children. Should OptiMA prove to be superior to ComPAS for the recovery of children MUAC < 115 mm but non-inferior to the current protocol that would pave the way for nutrition programming that is more efficient than current protocols and implementable at the level of the health post where weighing scales are available. The results of this trial should be interpreted together with the cost-effectiveness analysis to support policy decisions aimed at improving the coverage and quality of treatment.

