## Objectives

The principal objective aims to determine, 6 months after inclusion, whether the OptiMA strategy or ComPAS strategy leads to a favourable outcome which is non-inferior to what Niger standard protocol, in use in the same outpatient health facilities, provides. The definition of a favourable outcome is described in the “Study outcomes” section.

Two main secondary objectives for this trial are as follows. The first one is to determine whether the recovery rate of children with uncomplicated SAM according to the current WHO definition [14] (e.g. MUAC < 115 mm or WHZ < − 3 or bilateral oedema) managed under the simplified OptiMA or ComPAS strategies is non-inferior to that of the national standard protocol of Niger. The second one is to determine whether the recovery rate of children admitted with MUAC < 115 mm or oedema (+, ++) managed under the simplified OptiMA or ComPAS strategies is non-inferior to that of the national standard protocol of Niger.

Other secondary objectives include description and comparison between the three study arms of the following outcomes: cost-effectiveness analysis, RUTF consumption, relapse after nutritional recovery, non-response after outpatient follow-up, recovery, and success in children who present with both wasting and stunting at inclusion, and to describe the nutritional and clinical status of children hospitalised while enrolled in the study.

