### Sample size

We determined the sample size using an expecting success rate of 68% in each arm for the principal objective and a recovery rate of 82% and 74% for the main secondary objectives #1 and #2, respectively. These hypotheses were based on the results found in the pilot non-comparative cohort study implemented in the Mirriah district in 2019 (Personal communication, 2020). Recovery rates under OptiMA protocol were estimated at 91%, 70%, and 57% for children admitted with a MUAC between 115 and 124 mm and WHZ > − 3, those with SAM according to the WHO definition, and those with MUAC < 115 mm, respectively. In the OptiMA-Niger trial, recovery is defined throughout the 6-month follow-up which will increase these estimations. After having been discharged from this study, non-responders and a sample of recovered children were also seen 6 months after their exit in order to estimate a relapse rate. We estimated that children will be followed up on average 4 months after discharge with a relapse rate of 30%.

To demonstrate non-inferiority of the OptiMA or ComPAS strategies with standard protocol, we assumed a non-inferiority margin of 10%, the same as in other non-inferiority trials assessing simplified protocol [11, 13]. We reduced the test significant level (alpha) at 1.25 to consider the multiple testing [17], a power of 90% for the main objective and 80% for the 2 main secondary objectives were applied, and an inflation rate of 5% was used to account for unexploitable data. Calculations were performed using the SAS software (Proc Power TwoSampleFreq). For the principal objective, 568 children are required per arm, and 295 and 384 children per arm for the main secondary objectives #1 and #2, respectively.

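### The Discussion lets non-inferiority to OptiMA alone count as evidence for ComPAS, although every non-inferiority objective, the margin and the sample size use only the national protocol, and a later sentence contradicts it

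*Protocol article*

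**What the plan says.** The protocol article makes four statements that bear on this point.

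- **Objectives.** The principal objective asks "whether the OptiMA strategy or ComPAS strategy leads to a favourable outcome which is non-inferior to what Niger standard protocol" achieves. Both main secondary objectives also name the national protocol as comparator.
- **Sample size.** "To demonstrate non-inferiority of the OptiMA or ComPAS strategies with standard protocol, we assumed a non-inferiority margin of 10" per cent. No margin is given for ComPAS against OptiMA.
- **Discussion, positive conclusion.** "Should the ComPAS strategy be shown to be non-inferior to the current national protocol or OptiMA, this would provide the evidence". The sentence goes on to name a more efficient protocol as what that evidence would support. The *or* makes either comparator sufficient.
- **Discussion, negative conclusion.** "If non-inferiority of ComPAS and OptiMA versus national protocol will not be demonstrated in each objective, then dose reduction will not be advisable for these". The noun that closes the sentence is *children*.

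Between the last two, the Discussion describes one direct comparison of the two strategies. If both are non-inferior to the national protocol in children with MUAC < 115 mm, "the sample size will be sufficient to test whether OptiMA is in fact superior to ComPAS". That is a superiority test, and it is conditional on both strategies first passing against the national protocol.

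**The concern.** A non-inferiority conclusion is only as good as its reference. OptiMA is under test in this trial, and its standing against the national protocol is one of the questions to be answered. Showing that ComPAS is not much worse than OptiMA says nothing by itself about ComPAS against the national protocol. A comparison with OptiMA also has no objective, no margin and no share of alpha in the article.

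At stake is what may be concluded about ComPAS when its own test against the national protocol fails. One sentence of the paragraph allows a positive conclusion through OptiMA. A later sentence points the other way, but its scope is unclear.

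**Working it through.** **1. Which comparisons was the trial sized for?** Inputs from Sample size and Statistical analysis: equal rates of 68%, 82% and 74%; margin 0.10; one-sided alpha 1.25%; power 90%, 80% and 80%; inflation 5%. The formula is n = (z₁₋α + z₁₋β)² × 2p(1 − p) / 0.10².

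- Primary: (2.2414 + 1.2816)² × 2 × 0.68 × 0.32 / 0.01 = 540.1, so 541; × 1.05 = 568.
- Main secondary #1: (2.2414 + 0.8416)² × 2 × 0.82 × 0.18 / 0.01 = 280.6, so 281; × 1.05 = 295.
- Main secondary #2: the same multiplier × 2 × 0.74 × 0.26 / 0.01 = 365.8, so 366; × 1.05 = 384.

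These are the sizes given in the Sample size section. An alpha of 1.25% fits two comparisons with the national protocol (2 × 1.25% = 2.5%). A third non-inferiority test at that level would bring the sum to 3.75%. Power is not the obstacle: with 68% in every arm, ComPAS against OptiMA also has 90% power. The difficulty is the reference arm.

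**2. What the later sentence closes and what it leaves open.**

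- If it applies to every objective and rules out dose reduction when both strategies fail, a joint failure gives no positive conclusion.
- It ends on *these children*, after a sentence about MUAC < 115 mm. That may limit it to this subgroup, although its reference to each objective points the other way.
- *ComPAS and OptiMA* not demonstrated can mean that both fail or that either fails. If it means both, OptiMA passing lifts the restriction, and ComPAS can then be supported through OptiMA while failing against the national protocol.

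**3. How often that gap would matter.** Assumptions: about 540 evaluable per arm, unpooled Wald limits, one-sided 1.25%, and the 10-point margin borrowed for ComPAS against OptiMA. The national rate of 68% is the protocol's planning value; the OptiMA and ComPAS rates are illustrative.

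For a single comparison, P(non-inferior) = Φ((0.10 − d)/SE − 2.2414), where d is the true shortfall. At 68/65/62% (national/OptiMA/ComPAS):

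- ComPAS against national: d = 0.06, SE = 0.0290, P = 19%.
- OptiMA against national: d = 0.03, SE = 0.0287, P = 58%.
- ComPAS against OptiMA: d = 0.03, SE = 0.0293, P = 56%.

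The three comparisons share arms, so the joint probabilities were simulated (1,000,000 three-arm trials per scenario):

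| National/OptiMA/ComPAS | ComPAS passes against OptiMA but not national | of which OptiMA also fails against national | of which OptiMA passes (the gap) |
|---|---|---|---|
| 68/65/62% | 39.6% | 28.4% | 11.3% |
| 68/64/60% | 36.9% | 30.4% | 6.5% |
| 68/63/58% | 27.8% | 25.4% | 2.4% |
| 68/58/58% | 84.8% | 84.4% | 0.3% |

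In the first two rows ComPAS is truly within 10 points of the national protocol, so the gap there is a positive conclusion without the required test being passed, not a truly unacceptable arm being accepted. In the third row ComPAS lies exactly at the margin. Its chance of a positive conclusion would then be about 1.3% + 2.4% = 3.7%, against the intended 1.25%.

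**The case against.** The quoted sentence is forward-looking Discussion text. It fixes no test, margin or decision, and the Statistical analysis section contains no such rule. That section makes the other secondary analyses wait until non-inferiority is shown on the primary and main secondary outcomes, which the Objectives define against the national protocol. The one direct comparison the Discussion describes is also conditional on both strategies passing. The later sentence addresses joint failure, and the paragraph adds that results are to be read together with cost-effectiveness. On this view two words are loose and nothing else is wrong.

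Much of this stands. A reader might infer that ComPAS could be adopted when both strategies are worse than the national protocol. The documents do not support that: in the 68/58/58% scenario ComPAS passes against OptiMA in about 86% of trials, but nearly all of these are joint failures, which the later sentence covers if applied to all objectives. A reader might also chain two 10-point margins into a permitted 20-point shortfall. The article sets no margin for ComPAS against OptiMA, so it permits no such figure. Nor is the mention of community health workers an error; it describes where ComPAS could be implemented and does not claim that such delivery was tested.

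The objection does not remove the contradiction. The same paragraph gives two different answers when ComPAS passes only against OptiMA, and the analysis section does not settle it, since it speaks of two randomisation arms in a three-arm trial without naming them.

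**Conclusion.** The point holds as an internal contradiction with a limited practical gap. The Discussion treats non-inferiority to OptiMA as sufficient for ComPAS. The Objectives and Sample size sections provide for no such comparison, and a later sentence of the same paragraph ties the acceptability of dose reduction to the national protocol.

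If the later sentence is read as applying only when both strategies fail, the gap amounts to about 11% of trials at 68/65/62%, 6.5% at 68/64/60% and 0.3% at 68/58/58%. If it is read as applying when either fails, in every objective, the gap closes and only the inconsistency of wording remains. The percentages rest on assumed rates for the two strategies, about 540 evaluable children per arm and a borrowed 10-point margin. They illustrate size and do not predict the trial's result.

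**What to change.** Delete *or OptiMA* from the Discussion sentence, so that a positive conclusion for ComPAS requires non-inferiority to the national protocol. State that any ComPAS–OptiMA comparison is interpreted only after ComPAS has met that test. The later sentence should also say which children and objectives it covers, and whether it applies to each strategy separately.

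This changes wording only; sample size, data collection and alpha are unaffected. The cost is a narrower claim for ComPAS: similarity to OptiMA would no longer support it if it fails against the national protocol.
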